#### PJB steering committee and community-led program implementation

Approximately one and a half years prior to the launch of PJB, a dedicated PJB Steering Committee was created to further develop and finalize all aspects of PJB program design and implementation. The PJB Steering Committee is comprised of maternal and pediatric health practitioners, researchers focused on reproductive justice, leaders from community organizations, policy experts, and most importantly, LEEs from the HMH workgroup and/or each of the three target neighborhoods. Co-chaired by the PJB program manager and the LEE co-chair from HMH, the PJB Steering Committee has met monthly since its inception and uses CAN’s decision-making process to center LEE voices and votes.

Philly Joy Bank was finalized to provide $1,000 a month starting in the second trimester of pregnancy through 1 year postpartum for 250 pregnant people whose household incomes were less than $100,000 and who reside in the three target neighborhoods. By providing unconditional, unrestricted cash, PJB centers the dignity, power, and autonomy of participants to use the money as they see fit. Furthermore, to account for increased risks of fetal loss during the first trimester (22), yet maximize exposure to cash during pregnancy, the Steering Committee decided to restrict applicant eligibility to pregnant people in their second trimester of pregnancy.

Following the initial program design, the PJB Steering Committee embarked on a series of key implementation decisions. This included creation of a PJB Navigator position (to support applicants through the application process and to support participants in connecting with perinatal services), hiring and selection of the program manager, selection of disbursement, media, and storytelling vendors, and community-based outreach to recruit applicants for the program. The PJB Steering committee was not interested in selecting a disbursement vendor that tracked how recipients spent their cash as they felt that existing research had established that people who received unconditional cash spend their money to meet their family’s needs. The LEE co-chair was involved in all interviews and hiring processes, and the same consensus-based decision-making processes were used to interview and select final vendors for collaboration and support of PJB.

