#### Application to PJB

Applicants for PJB are recruited using a three-tiered recruitment process, which was developed by the PJB Steering Committee: (1) referral and advertisement at healthcare providers in each neighborhood; (2) referral and advertisement at neighborhood community sites (social services offices, libraries, etc.); and (3) via social media, including the Philly Joy Bank website^2^. Individuals interested in applying for the PJB lottery do so via the PJB website, where they complete their application and receive assistance with submitting their application, if needed. Individuals can apply for the PJB lottery if they are: (a) 18 years or older; (b) between 12 and 24 weeks pregnant; (c) self-attest to household income of ≤100 K per year; and (d) live in one of the three target neighborhoods. The PJB program manager and navigator confirm each applicant’s eligibility for PJB before applicants are recruited to participate in the evaluation research study or entered into the lottery. See Figure 2 for a visual of the timeline of PJB application, lottery selection, and research study enrollment.

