### Part 4. Evaluation of PJB

#### Research study enrollment and retention

Prior to lottery selection, all individuals who are eligible for the lottery are also eligible (but not required) to participate in the evaluation research study. Individuals learn about the opportunity to join the study from community researchers (CR) immediately after the PJB team confirms their eligibility and prior to lottery selection. The CRs emphasize to applicants that study participation is voluntary -- lottery selection is not contingent upon participation in the study. Individuals who are interested in participating in the study provide informed consent via phone and either complete the baseline survey the same day or schedule a time for baseline survey completion within the next week. At the time of the baseline survey, approximate dates for the follow-up surveys are scheduled based on the participant’s estimated date of delivery (EDD). At enrollment into the study, participants are asked to share their phone number and their address so that we may remind them of future appointments.

Following approaches the research team has used in other studies, CRs check in with participants via phone, text message or email at a minimum of four time points to maximize retention. First, CRs do a phone check-in with participants 1 month prior to delivery and also send out a short e-newsletter around the EDD to keep participants passively engaged and foster a sense of community and commitment. Second, CRs do a text or call check-in with participants 1 month after estimated delivery to ascertain actual delivery date. CRs repeat the phone check-in approximately 1 month prior to all postpartum visits to confirm or (re)schedule the follow-up survey. Participants who miss their scheduled appointment are contacted within one business day. At least four attempts are made to contact the participant by phone, text or email, using multiple contact times to increase success (am/pm/weekend).

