#### Quantitative data collection

Quantitative data collection takes place at enrollment (12–24 weeks gestation) and at 6 and 12 months postpartum (Figure 3). Participants in both groups (i.e., cash + care and care only) complete the baseline survey prior to receiving the cash disbursement, financial counseling, or care services. Survey data is collected through REDCap, a secure, web-based application that complies with HIPAA regulations. All data collection procedures follow approaches used in other local studies. Each survey is administered via an interviewer over the phone. Each question is read to the participant; responses are recorded on a tablet with a secure internet connection. All data management standards reflect the goal of reproducible research. To reduce data entry errors and omissions, we take advantage of REDCap’s built-in quality control functions. Data integrity is aided by the system’s automated logging of all input and edits. After each survey is complete, CRs send the participant a gift card (electronically or by text) and a community resource guide. Participants receive $50 for completion of the baseline survey, and the amount is increased by $25 for each subsequent survey.

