#### Quantitative measures

Outcomes will come from multiple data sources. We will draw on PJB routine monitoring data to assess feasibility. Self-report outcomes (including reports on acceptability and satisfaction) will come from surveys. Finally, for engagement in prenatal care and birth outcomes, with consent from participants and permission from the Pennsylvania Department of Health, Bureau of Health Statistics and Registries, we will obtain individually matched birth records of study participants.

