#### Outcomes

Low birth weight will be extracted from the birth record and defined as an absolute weight of <2,500 g regardless of gestational age (27). Preterm birth will be extracted from the birth record and defined as birth prior to 37 weeks gestation (27).

Depression will be assessed using the Edinburgh Postnatal Depression Scale (EPDS), a measure validated for use during and up to 24 months after pregnancy (28–31). The scale consists of 10 items scored on a 4-point Likert scale which ask about common depressive symptoms experienced in the prior week. We will characterize this primary outcome using a continuous score because subclinical symptoms can impact functioning (32, 33). Additionally, we will characterize probable depression (yes vs. no) using a cut-off score of ≥11 (34). Anxiety will be assessed using the Generalized Anxiety Disorder scale-7 (GAD-7) score (continuous) which is a reliable and validated measure for use during and after pregnancy. The GAD-7 consists of 7 items scored on a 4-point Likert scale which ask about common anxiety symptoms in the prior 2 weeks (range 0–21).

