Explore the preliminary impact of PJB on parental mental health and prematurity. The purpose of the PJB is to reduce disparities in birth outcomes. Given the limited numbers of participants in this pilot program and evaluation study, however, we are underpowered to examine such disparities. Consequently, birth outcomes are included as exploratory analysis for potential signals of GI impact. Another important outcome for the PJB evaluation study is perinatal depression, which we do have sufficient statistical power to examine. Perinatal depression is also associated with adverse birth outcomes and can be a marker for perinatal health.

To investigate post-baseline differences in continuous EPDS depression score in the cash + care and care groups, our primary analyses will use mixed effects regression models with fixed effects for time (baseline, 6 months postpartum and 12 months postpartum), group, and the interaction between time and group and random participant-level intercepts. Using these models, we will estimate and report the average difference in depression score between groups over follow-up with 95% confidence intervals. We will also characterize outcome patterns over time by presenting estimated mean outcomes at each time point individually. We will use the same approach to examine post-intervention differences anxiety score. In secondary analyses, we will examine differences in infant birthweight and preterm birth in the cash + care vs. care groups using logistic regression. Birthweight and gestational age at birth will be determined using data from birth records and classified as low birthweight <2,500 grams (y/n) and preterm birth <37 weeks (y/n). We will examine the sensitivity of our findings to the inclusion of key potential confounders in our models, including SES and pregnancy-related variables (e.g., gravidity, parity, maternal health conditions).

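### Low birthweight and preterm birth come only from birth records and loss after the lottery is not a listed outcome, so these exploratory comparisons may rest on a set formed after cash begins

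*Protocol article*

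**What the plan says.** - **Entry.** Under Application to PJB, applicants must be "between 12 and 24 weeks pregnant". Under Quantitative data collection: "Quantitative data collection takes place at enrollment (12–24 weeks gestation) and at 6 and 12 months postpartum". The lottery and the start of cash follow the baseline survey.
- **Source of birth outcomes.** Under Quantitative measures: "we will obtain individually matched birth records of study participants". Under Outcomes: "Preterm birth will be extracted from the birth record and defined as birth prior to 37 weeks gestation"; low birthweight (<2,500 g) has the same source. Aim 3 repeats it: "Birthweight and gestational age at birth will be determined using data from birth records". The two groups are then compared by logistic regression.
- **Fetal loss.** It appears once, in the section on the PJB steering committee, as a reason for admitting only second-trimester applicants: "to account for increased risks of fetal loss during the first trimester (22), yet maximize exposure to cash during pregnancy". It is not among the outcomes in Part 4.
- **Contact around delivery.** Under Research study enrollment and retention: "CRs do a text or call check-in with participants 1 month after estimated delivery to ascertain actual delivery date". The article does not link this contact to the birth outcomes.
- **Status.** Aim 3 calls the birth outcomes exploratory and concedes low power for disparities in them. The powered outcome is the EPDS depression score.

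**The concern.** The lottery balances the groups among everyone who enters. That balance carries over to an outcome only if the outcome is defined for everyone who enters, or if the set left out is unrelated to the lottery result. Between 13 weeks (entry at 24) and 25 weeks (entry at 12) separate entry from the 37-week threshold. A pregnancy that ends in loss in that time presumably yields no matched birth record and so leaves both numerator and denominator.

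Loss and very early birth compete. If cash kept some pregnancies going to an early birth, those births would enter the cash group's numerator while the matching losses in the care-only group stayed out of sight. Recorded preterm birth would then rise in the group that did better. An effect in the opposite direction could be hidden in the same way.

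Neither stated safeguard covers this. The Aim 3 sensitivity analysis adds confounders such as socioeconomic status and parity. The general statement on missing data does not mention losses, and a loss is a competing event rather than an unrecorded birthweight. The matter is also partly one of data capture: an analysis plan cannot recover an outcome that was never asked about.

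**Working it through.** **1. The plan's own power figure.** It concerns the EPDS only; none is given for birth outcomes. Inputs from Power and sample size: 164 and 117 participants, SD 6.24, two observations each, two-sided alpha 0.05, 80% power, within-participant correlation ρ.

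Detectable difference = (1.960 + 0.842) × 6.24 × √[(1 + ρ)/2] × √(1/164 + 1/117)

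- ρ = 0.5, 0.4, 0.3: 1.83, 1.77, 1.71 (stated 1.8, 1.8, 1.7).
- 123 and 88 after 25% dropout, ρ = 0.5: 2.11 (stated 2.1).

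The figures reproduce, and nothing below touches them.

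**2. Inputs for the artifact.** The article gives neither a loss rate nor a preterm rate, so these are assumptions:

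- p = 14.5% preterm among births. This is a stand-in taken from the 14.1–14.8% low-birthweight range under Study setting.
- L = risk of loss after the lottery without cash: 2%, with a range of 1–5%.
- a = share of losses averted by cash: 25–100%.
- q = share of averted losses born preterm: 50–100%, and also 14.5% (the background rate).
- No effect of cash on prematurity other than through averted losses.

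**3. Formulas.**

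- Recorded preterm birth, cash group = [(1 − L)p + L·a·q] / (1 − L + L·a)
- Artifact = that minus p = L·a·(q − p) / (1 − L + L·a)
- Loss or preterm among all pregnancies: care only = L + (1 − L)p; cash = L(1 − a) + (1 − L)p + L·a·q

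**4. Results at L = 2%.**

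| Averted (a) | Born preterm (q) | Recorded preterm, care vs cash | Artifact (points) | Loss or preterm, care vs cash |
|---|---|---|---|---|
| 50% | 100% | 14.5% vs 15.4% | +0.9 | 16.2% vs 16.2% |
| 100% | 100% | 14.5% vs 16.2% | +1.7 | 16.2% vs 16.2% |
| 50% | 50% | 14.5% vs 14.9% | +0.4 | 16.2% vs 15.7% |
| 50% | 14.5% | 14.5% vs 14.5% | 0 | 16.2% vs 15.4% |

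First row written out: (0.98 × 0.145 + 0.01)/0.99 = 0.1521/0.99 = 15.4%, an odds ratio of 1.07. In the third row the sign differs by denominator: recorded births lean against cash, all pregnancies lean toward it.

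With q between 50% and 100%, the artifact runs from +0.1 (L = 1%, a = 25%, q = 50%) to +4.3 (L = 5%, a = 100%, q = 100%).

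**5. Against sampling error.** Half-width of the 95% interval = 1.96 × √[0.145 × 0.855 × (1/164 + 1/117)] = 1.96 × 0.0426 = 8.4 points. At 2% loss, 281 × 0.02 ≈ 6 losses would be expected without cash, of which 117 × 0.02 ≈ 2 in the care-only group.

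**The case against.** The strongest reply is that this is an omission in a condensed article. How losses enter a denominator is often settled in a full protocol or analysis plan, and neither is shown. Low birthweight and preterm birth are by nature outcomes of births, so *loss or preterm* answers a different question. The outcomes are exploratory, and the artifact is too small to see with 281 participants. All of this limits the weight of the point. It does not remove it, because the article does fix the source of the outcomes, lists no loss outcome, and offers no comparison that keeps everyone who entered.

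Several stronger readings are tempting and are not supported:

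- A reader might infer that fetal loss is acknowledged as a risk for enrolled participants. The article names it for the first trimester only, as something the eligibility window is meant to reduce. Loss after 12 weeks remains possible, but the article does not discuss it.
- A reader might infer that losses certainly drop out. The article does not say what the matched records cover and does not restrict the outcomes to live births. Exclusion is an inference.
- A reader might infer that the check-in asks for nothing but the delivery date. Its stated purpose is the delivery date, but the script and the survey instruments are not shown.
- A reader might infer a bias large enough to reverse the findings. At 2% loss, even +1.7 points requires cash to avert every loss and every one to be born preterm.

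**Conclusion.** The point holds as a modest gap in the exploratory analyses. Followed as written, the article compares low birthweight and preterm birth among participants with a birth record, presumably a set formed after cash begins, and gives losses no stated place in either group. The direction of the possible artifact is clear: recorded preterm birth in the cash group rises whenever averted losses are born preterm more often than the background rate. Its size rests wholly on assumed rates. At 2% loss it lies between zero and +1.7 points, with +0.9 as a middle case; even the extreme corner of the assumed range (+4.3) is about half the 8.4-point half-width. The EPDS power figures stand. This is a cheap improvement, not a flaw in the main result.

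**What to change.** 1. At the existing check-in one month after the due date, record the pregnancy outcome: live birth, or loss with gestational age. Ask again at the 6-month contact for those missed. Program enrollment closed in March 2025, so participants already past the check-in would be asked at their next scheduled contact.
2. Report losses by lottery group, with all enrolled participants as the denominator.
3. Beside the birth-record analysis, add *loss or birth before 37 weeks* and *loss or birthweight <2,500 g* among all enrolled, labeled as exploratory sensitivity analyses.
4. State what the matched birth records cover. If the full protocol or analysis plan already deals with losses, a sentence saying so is enough.

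The cost is one question in a contact already planned, one descriptive table and two logistic models. The downsides are a sensitive question that needs careful wording, reliance on self-report, and very few events, so the added models will be imprecise.

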#### Power and sample size

This study is powered on detecting a difference in EPDS depression score between the cash + care vs. care groups during the 6- to 12-month postpartum period (Aim 3). Preliminary data from eligible participants suggest a mean Edinburgh Postnatal Depression Scale (EPDS) score of 10.45. Table 1 presents the estimated minimum detectable differences in depression scores between the two groups given a total of 281 participants with 164 in the cash + care group and 117 in the care-only group. We assumed two observations per participant (6- and 12-months postpartum) after initiation of the cash + care or care only interventions, a standard deviation of 6.24 (based on preliminary data), a significance level (two-sided alpha) of 0.05, and a within-participant correlation ranging from 0.3 to 0.5. For example, we achieve 80% power to detect a 1.8 point mean difference in EPDS score between the care-only group and the cash + care group, given a within-participant correlation of 0.5. A clinically meaningful difference on the EPDS scale is defined as a change of 4 points for improvement (43). Given our current sample size, we will have sufficient power to detect these clinically significant differences. Even with a projected 25% dropout rate for both groups (e.g., 123 in the cash + care group and 88 in the care-only group), we will still be able to detect a minimum difference of 2.1. All power calculations were carried out using PASS (44).

**Table 1 tab1:** Estimated minimum detectable differences in depression scores.

Within-participant correlation	Mean difference
0.5	1.8
0.4	1.8
0.3	1.7

#### Overview of participatory qualitative research methods

Longitudinal participatory arts-based narrative methods, hereafter participatory research, will be used to identify potential mechanisms affecting mental health and infant health from the perspectives of PJB recipients (45, 46). Findings will also be used to contextualize the quantitative findings. Per the tenets of participatory research, involving community members who are the focus of research throughout the entire research process enhances the identification of the research topic, the research process, and the impact of findings (47). Thus, the participatory research component has been co-designed with the members of the CAB, and participatory methods will be applied to the data collection, analysis, and dissemination of findings. The reflexive longitudinal participatory design prioritizes opportunities for (a) participant feedback in all aspects of the research process, (b) building ongoing relationships with participants, and (c) ongoing analysis with participants throughout data collection (48). Further, relationship-building between participants and group cohesion are inherent to the proposed methods. Relevant to the study’s focus on structural racism and financial insecurity among Black birthing people, participatory research methods have been used in such areas as structural and neighborhood level factors affecting Black mothers’ physical and mental health (49–51).

#### Participatory data collection

The data collection will occur in two phases: during pregnancy (phase I), and 6 months postpartum (phase II). Phase I includes six 2-h weekly in-person group sessions. Phase II includes 2 three-hour sessions. Because cohesion will have been established during Phase I, and because participants will have an infant/child, Phase II will be shortened to two 3-h sessions to maximize retention. Sessions will occur at a site chosen in collaboration with participants, with meals, transportation and childcare included and will likely occur during weekends to maximize participation. Participants will be compensated for their time ($25/h). All sessions will be recorded with consent. Sessions will be led by the LEEs from the CAB, with guidance from the co-principal investigator ([name]). We will use the methodological framework of *critical narrative intervention* in this study and envision using a blend of two participatory arts-based research processes – Photovoice and Cellphilms (52–54). In *Photovoice*, participants use photographs and other visual representations of their daily lives to explain their lived experiences (54). Photovoice has been used with other racialized birthing populations (55) and provides an opportunity for participants to share their opinions about and analyze health issues that may be silenced by societal, clinical, community, and family structures. *Cellphilms* are brief films made on cellular devices by participants in response to prompts that tap into the individual’s already well-developed expertise in analyzing their everyday lives (52). In Photovoice and Cellphilms, participants define their own photo prompts, conduct data collection (photography, filming), and engage in group thematic analysis based on their productions (photos, short films). Both methods use Storytelling, shown to preserve a collective memory and share historical knowledge (55–57). We will use Photovoice/Cellphilm methods to obtain nuanced pictures, videos, and corresponding narratives of participant’s lives during and after receipt of PJB. Subsidies will be made available to participants to account for any lack of access to data coverage and/or cell phone. All narrative and photo data will be stored in a secure location and all identifying information will be removed.

Phase I (during pregnancy) will include 6 sessions as is typical in participatory research using Photovoice/Cellphilms (52, 54). As seen in Table 2, Session 1 will involve identity and community building to establish rapport between participants and the research team ([name], LEEs), as well as familiarizing the group with the ethical issues involved in photographing/filming others, the potential risks to participants in taking photos/videos and how to minimize these risks, the practice of giving photos back to the participants, and a review of photography techniques using a cell phone camera (53). Participants will receive guidance on how to generate photos/Cellphilms in response to the prompts to explore if/how GI influences (1) perceptions of financial security; (2) stress; and (3) ability to meet basic needs. At the end of Session 1, participants will collectively select one prompt as the focus of the next week’s assignment. Participants will take photos/videos of the prompt while going about their weekly activities and will use the SHOWED method to describe each photo/Cellphilm (52–54). The SHOWED method consists of five questions that lead participants through the photos/Cellphilms: (1) What do you see here?; (2) What is really happening here?; (3) How does this relate to your life?; (4) Why does this situation, concern, or strength exist?; and (5) What can we do about it? At each subsequent session (Sessions 2–4), group discussion, or “debriefs” will provide insight into the influence of GI on the aforementioned prompts. In each session, participants will also explore the mechanistic relationships between prompts (e.g., perceptions of financial security, stress, ability to meet basic needs) with (a) mental health and (b) their relationship to their child. Session 5 will involve group thematic analysis and Session 6 will be a group celebration.

**Table 2 tab2:** Participatory research sessions, by phase.

	Session 1	Session 2	Session 3	Session 4	Session 5	Session 6
Phase I	- Introduce activities - Assign prompt #1	- Debrief prompt #1 - Connect prompt to outcomes - Assign prompt #2	- Debrief prompt #2 - Connect prompt to outcomes - Assign prompt #3	- Debrief prompt #3 - Connect prompt to outcomes	- Group thematic analysis	- Celebration (completion of Phase I)

	Session 1	Session 2
Phase II	- Reconnect - Debrief prompts #1–3 (assigned ahead of time) - Connect prompts to outcomes	- Group thematic analysis - Celebration (completion of participatory study)

In Phase II (6 months postpartum), we will ask participants to reflect on how their lives have changed during PJB (Phase II) using Photovoice/Cellphilm methods, especially in relation to the aforementioned prompts. For these sessions, participants will be asked to revisit prompts in advance and bring photos/Cellphilms to the debrief. Participants may share how the cash was used in the photovoice sessions in response to prompts. In Session 1, we will debrief using the new material. As part of the debrief, we will incorporate visual and narrative data from prior phases, as connecting data across time allows us to understand change more than any single time point (48). Group discussion will also include connecting prompts to outcomes. Session 2 will involve group thematic analysis.

